### Outcomes

#### Primary outcomes

Considering that the main goal of this study is to determine that vHIE intervention performed with the own virtual body (1PP) has a beneficial effect on cognitive executive functions, the primary outcome of this study is the Stroop task (i.e. the cognitive domain), specifically the two related measurements (RT primarily and ER secondarily). The Stroop task is considered the primary outcome here because it is widely known as a measure for executive brain functions [21, 55]. As a key effect of the Stroop task, we will consider the so-called “Stroop interference” as the (average of incongruent trials– average of neutral trials) contrast, which is assumed to represent Stroop interference, for both RT and ER in each condition (1PP and 3PP).

Specific timepoints (before and after the vHIE) will be considered, but the main comparison in order to find a significant effect of vHIE on cognitive functions will be 1PP versus 3PP.

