### Sample size

Considering that the main outcome of this study is the RT of the Stroop task (which is claimed by many to be one of the indicators of executive performance), which typically has a moderate effect, we calculated a sample size of 28 individuals (with α error probability set at 0.05 and power set at 0.8). We decided to recruit 30 participants to eventually control for drop-off.

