#### Stroop task’s RT and ER

The second phase of the data analysis concerns the data collected before and after every IVR intervention, i.e. the results necessary to confirm our main hypothesis (the efficacy of IVR training on cognition).

As previously mentioned, in the Stroop task we will include two measurements, RT and ER: the (incongruent – neutral) contrast, which is assumed to represent Stroop interference, will be calculated. Both (RT and ER) will be analyzed by means of a repeated-measures ANOVA with TIME (before, after) and CONDITION (1PP, 3PP) as within-subject factors. As supplementary analysis, we will check for eventual differences between the two sessions considering only the Stroop task before the vHIE (predicting not differences). According to our hypothesis, we predict finding a shorter RT and lower ER after the vHIE in 1PP compared to 3PP.

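### The primary test of RT interference is not fixed: the stated main comparison, the ANOVA and the hypothesis point to different terms, and none adjusts for the pre-vHIE scores

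*Protocol article*

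**What the plan says.** Under Outcomes, Primary outcomes, the protocol article makes Stroop interference (incongruent minus neutral) the primary measure, with RT ahead of ER. It mentions the before and after timepoints and then states that "the main comparison in order to find a significant effect of vHIE on cognitive functions will be 1PP versus 3PP".

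Under Statistical analysis, in the subsection on the Stroop task's RT and ER, both measures go into a "repeated-measures ANOVA with TIME (before, after) and CONDITION (1PP, 3PP) as within-subject factors". The prediction there is placed after the intervention: "we predict finding a shorter RT and lower ER after the vHIE in 1PP compared to 3PP". Pre-vHIE scores enter as one level of TIME and in a supplementary check that the two sessions start alike. No baseline covariate is mentioned.

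Two other places bear on the point. The Correlations subsection writes out a full difference-in-change contrast, but only to relate Stroop results to cortical activation or mood. The Discussion expects improvement after 1PP and none after 3PP.

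**The concern.** The article offers more than one test of a single claim. The CONDITION main effect matches the literal wording of the main comparison. The TIME × CONDITION interaction matches the idea of a different change in the two conditions. A comparison of post-vHIE scores alone matches the wording of the prediction. These tests have different estimands or different precision, so the primary conclusion could depend on which one is reported.

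The CONDITION term is a poor match to the hypothesis, because scores taken before a session's vHIE cannot carry that session's effect. The interaction is a proper test, but it subtracts the pre-vHIE difference in full (slope 1). Each interference score is a difference between two means of 10 trials, so it may well be noisy, and a slope below 1 is plausible. At stake are a clear primary result and sensitivity in a trial of 30 people.

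**Working it through.** **The plan's own figure.** The Sample size section says "we calculated a sample size of 28 individuals", "with α error probability set at 0.05 and power set at 0.8", for an outcome "which typically has a moderate effect". Sidedness, numerical effect size, test and correlation are not stated. If moderate is read as d = 0.5, a paired t-test needs 34 people two-sided or 27 one-sided. A repeated-measures ANOVA with f = 0.25 and correlation 0.5 needs 34 for two measurements, 28 for three and 24 for four. With two measurements and correlation 0.6 it needs 28. So 28 can be reached in several ways, but it cannot be tied to a term of the planned ANOVA and does not show which term was meant.

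**Set-up.** Let Dpre and Dpost be one person's 1PP−3PP difference in RT interference before and after the vHIE. Assume that both have variance V and that their correlation is β (with equal variances it is also the slope of Dpost on Dpre). Assume that the true effect δ is present in Dpost only.

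| Test | Expected estimate | Variance per person |
|---|---|---|
| CONDITION main effect | δ/2 | V(1+β)/2 |
| TIME × CONDITION | δ | 2V(1−β) |
| Dpost adjusted for Dpre | δ | V(1−β²) |

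**Dilution.** The mean of Dpre and Dpost has expectation (0 + δ)/2 = δ/2. With δ = 0.50, simulation (20,000 runs, n = 28) gave 0.25 for CONDITION and 0.50 for the other two.

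**Interaction against adjustment.** The variance ratio is 2V(1−β) / [V(1−β)(1+β)] = 2/(1+β). The share of information lost is 1 − (1+β)/2 = (1−β)/2:

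- β = 0: ratio 2.00, loss 50%
- β = 0.3: ratio 1.54, loss 35%
- β = 0.5: ratio 1.33, loss 25%
- β = 0.7: ratio 1.18, loss 15%

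With the slope estimated at n = 28, the simulated adjusted-to-interaction variance ratios were 0.52, 0.67, 0.77 and 0.90, against 0.50, 0.65, 0.75 and 0.85 by formula. The small excess is the price of estimating the slope.

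**Power at a fixed effect.** Assumptions: δ = 0.5 SD of Dpost, two-sided 0.05, no sequence term. Entries are CONDITION / interaction / adjusted.

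| β | Power at n = 28 | N for 80% power |
|---|---|---|
| 0 | 44% / 44% / 72% | 65 / 65 / 34 |
| 0.3 | 35% / 58% / 76% | 84 / 46 / 31 |
| 0.5 | 31% / 72% / 84% | 97 / 34 / 26 |
| 0.7 | 28% / 91% / 95% | 109 / 21 / 19 |

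**Second scenario, with a sequence term.** Here n = 30, the interaction's standardised effect is held at 0.5, the between-session correlation is 0.4 and the same-session correlation runs from 0.4 to 0.7. Then β = (0.4−0.4)/(1−0.4) = 0 to (0.7−0.4)/(1−0.4) = 0.5. Simulated power was about 0.76 for the interaction, 0.95 falling to 0.85 for the adjusted test, and 0.75 falling to 0.34 for CONDITION. Type I error was about 5% for all three. Because the interaction's effect is held fixed here, the raw effect shrinks as β rises. The table above is therefore the fairer comparison across β.

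**The case against.** The strongest reply is that the article never names the CONDITION main effect as the deciding test. In the Primary outcomes section, 1PP versus 3PP may simply name the two conditions. The Stroop prediction, the contrast in Correlations and the Discussion all fit the interaction, which is valid and unbiased. A statistical analysis plan that is not shown might name the term. Most of this stands. A reader might infer that the trial will be decided on a term containing pre-vHIE data, but the documents do not say so. What remains is that the article does address its primary comparison, and in words that do not match its model or its hypothesis. That is more than a detail left for later.

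Three further inferences are tempting and should not be drawn:

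- **That a chance baseline difference makes a positive CONDITION result spurious.** Order is randomised, so such a difference is ordinary sampling error already in the test's variance, and simulated type I error stayed at about 5%.
- **That three open F-tests give a 14% false-positive chance** (1 − 0.95³ = 0.143). TIME does not compare the conditions and cannot decide the trial. Two candidate terms give 1 − 0.95² = 0.0975, and only if whichever is significant were reported, which the article does not propose.
- **That the interaction wastes half the information.** Half is the bound for β ≥ 0, reached only at β = 0. At 0.7 the power gain from adjustment is small (91% to 95%).

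Preferring adjustment to the interaction is a matter of efficiency. The interaction would not be an error.

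**Conclusion.** The point holds as a failure to fix the primary test, together with a missed and nearly free gain in precision. The Primary outcomes section and the Stroop analysis subsection need to be reconciled. If CONDITION were used, an effect present only after the vHIE would be halved, and power at n = 28 would be 44% to 28% for β from 0 to 0.7. If the interaction were used, the test would be sound but would lose 50% to 15% of the information over the same range.

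These sizes rest on assumptions that the documents do not supply: the value of β, equal variance before and after, an effect of 0.5 SD, two-sided testing, and no effect of the vHIE in the pre-vHIE scores. Naming the test is the necessary part. Baseline adjustment is the recommended choice of test.

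**What to change.** In both the Primary outcomes section and the Stroop analysis subsection, name one primary test: the 1PP−3PP difference in post-vHIE RT interference, adjusted for the pre-vHIE 1PP−3PP difference and for sequence.

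In practice, regress each person's post difference on the pre difference and on sequence, and test the intercept. Two details of coding matter:

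- Leave the pre difference uncentred, so that the intercept is the effect at a pre difference of zero.
- Code sequence +½ and −½. With 0/1 coding the intercept absorbs the period effect, and the Discussion itself allows for a repetition effect. Under the null with a period effect of 0.4 SD, the 0/1 version rejected 12% to 26% of the time; centred coding stayed at about 5%.

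Report TIME × CONDITION as a sensitivity analysis, and state that the CONDITION main effect will not be interpreted as an intervention effect. If the investigators prefer not to adjust, the minimum is to name TIME × CONDITION on RT interference as primary.

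The cost is wording and two degrees of freedom (residual 30 − 3 = 27, against 30 − 1 = 29 for the interaction). It needs no new data, visits or participants.

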#### Secondary outcomes

Secondary outcomes are the data extracted from the fNIRS recording, as a neural counterpart of the behavioral measurements. We will focus specifically on O2Hb changes before and after the vHIE in the two conditions (1PP and 3PP).

In addition, we will examine the relation between Stroop task and the induced cortical activation, by means of a correlation between behavioral data from the Stroop task (RT and ER) and optical data from fNIRS. For each trial of the Stroop task (neutral, congruent, and incongruent), we will average the O2Hb data for 2 s before, 2 s during, and 10 s after the presentation of the stimulus (expecting a peak at 4–11 s after the display); also in this case, we will obtain the Stroop interference by subtracting (incongruent-neutral) O2Hb data. As for the other outcomes, the main comparison to test our hypothesis will be between 1PP and 3PP.

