### Randomization of interventions

The two intervention conditions will be administered to all participants in two separate sessions (one week apart). Random assignment to the first intervention using an online program (http://www.graphpad.com/quickcalcs/index.cfm) will take place [43]. Each participant is first assigned to a condition non-randomly (the random number generator is seeded with the time and the day). The assignment of each individual is then swapped twice (to make sure it is really random) with the condition assignment of a randomly chosen participant. Half of the participants (15 individuals) will perform the experimental condition first, while the other half will perform the control condition first. The sequence, and with it the assignment to the first intervention condition, is hidden from the researcher that enrolls the participants until the intervention starts to avoid biases; once the intervention begins, the sequence is no longer blinded from anyone.

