#### Correlations

The crucial correlation for our hypothesis concerns the relationship between Stroop task and fNIRS data: we will first investigate the cortical regions mainly activated during the Stroop task before the vHIE in both intervention conditions, as a baseline reference. Then, the (incongruent – neutral) contrasts for the two intervention conditions will be averaged as substrates for ROI analysis. The (incongruent – neutral) contrast for RT and ER with O2Hb changes in all ROIs will be treated with a repeated-measures ANOVA considering as factors intervention condition (1PP and 3PP) and time (before and after the vHIE).

In addition to that, as described in previous studies, we will examine the relation between Stroop data and cortical activation or TDMS results in a binominal manner [22, 49]: for each variable the following contrast will be calculated {[(incongruent – neutral) of after vHIE] – [(incongruent – neutral) of before vHIE] in 1PP condition} – {[(incongruent – neutral) of after vHIE] – [(incongruent – neutral) of before vHIE] in 3PP condition}. Both values will be subjected to the McNemar test to examine the correspondence between the two incidences [66].

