These results would contribute on different levels: from a theoretical perspective, this study would be another proof that the illusion of ownership over the virtual body is extremely effective and can be manipulated in order to arise effects on different levels (perhaps motor and cognitive). The simple fact that it is possible to show some effects consequent to the virtual illusion, comparable to the real ones, means the virtual movements are as effective as the actual ones. Our idea is that the SoBO (here the main variable manipulated through the perspective) can drive other aspects, such as motor function, and those, in turn, can drive others, such as cognitive functions. Theoretical models of motor control should clearly state the body and the sense of body ownership as a variable that can significantly affect the resulted action [68, 69].

From a clinical perspective, these results will have interesting applications: as previously mentioned, the intervention presented here can be very useful for sedentary people or those suffering from cardiopathy to start physical activity in a totally safe and entertaining way, or combining cardio or power exercise, and the IVR training, maximizing the efficacy of both on somatic and cognitive terms. In more extreme situations, patients with motor disorders can perform the virtual training but with the same beneficial effects as physical training [70].

However, this study has some limitations. All participants have to repeat the Stroop task four times (before and after the two IVR sessions). This could have a learning effect, or an effect due to the repetition itself, as a negative consequence. To avoid this, we will randomize the order in which the intervention conditions will be administered, but it is still possible to have a repetition effect. Another potential limitation concerns the control conditions of the intervention: several previous studies using IVR exploit the 3PP as a control condition. In some cases, it seems to have a sort of effect, although the reported effect is smaller than the one of the experimental condition. Finally, a difference between the previous study with a similar design and the current one concerns the type of intervention: in Kujach et al. [17], the training consists of a cycling exercise, while in our study we decided on a running exercise in order to be as consistent as possible with other previous studies with similar IVR setup [33].

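### The per-person contrasts used to relate Stroop and fNIRS changes pool the two session orders, so session-dependent change in both measures could create or mask an association; removing order costs one degree of freedom

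*Protocol article*

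**What the plan says.** Three parts of the protocol article bear on this point.

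- **The association.** Secondary outcomes plans to link behaviour and brain signal "by means of a correlation between behavioral data from the Stroop task (RT and ER) and optical data from fNIRS". It does not say which per-person values enter that correlation. The second paragraph of the Correlations section adds that "we will examine the relation between Stroop data and cortical activation or TDMS results in a binominal manner". It states that "for each variable the following contrast will be calculated", and the formula that follows is the (incongruent minus neutral) change from before to after vHIE in 1PP, minus the same change in 3PP. The test named there is McNemar: "Both values will be subjected to the McNemar test to examine the correspondence between the two incidences".
- **The order.** Under Randomization of interventions, "Half of the participants (15 individuals) will perform the experimental condition first"; the other 15 start with the control condition. No order, session or sequence term appears in any of these analyses. The Stroop model is "a repeated-measures ANOVA with TIME (before, after) and CONDITION (1PP, 3PP) as within-subject factors".
- **Repetition.** The Discussion accepts that four Stroop administrations per person may bring learning. It offers random order as the remedy: "we will randomize the order in which the intervention conditions will be administered, but it is still possible to have a repetition effect".

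**The concern.** Balancing the order 15/15 protects the average 1PP-minus-3PP difference, because an order effect raises it in one half and lowers it in the other. It does not protect an association across people. If order shifts the Stroop contrast and also shifts the O2Hb contrast, order is a common cause of both, and pooling the two groups makes them covary even when nothing links brain and behaviour within a person.

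The planned checks would not reveal this. The section on Stroop RT and ER compares only the pre-intervention Stroop results between sessions, and the TDMS section compares only pre-intervention mood. A session difference in the before-to-after change is invisible to both.

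At stake is the reading of a positive result as a neural counterpart of a cognitive gain from embodiment, or of a null result as absence of one. The artefact can go in either direction, depending on the signs of the two order effects.

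**Working it through.** The documents give no figure for this association, so there is no stated value to reproduce.

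**Inputs from the protocol article:** 30 participants, 15 per order; four Stroop administrations; the contrast as defined in the Correlations section. **Assumed:** the size of the order shift q (0 to 1.0 SD), because no practice effect is reported; a Pearson test at two-sided 5%, because the type of correlation is not stated; and that the correlation is run on the contrasts of the Correlations section.

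**Step 1: the order term.** Let c1 and c2 be the within-session changes due to repetition in sessions 1 and 2, and τ the condition effect.

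- 1PP first: D = τ + (c1 − c2) + e
- 3PP first: D = τ − (c1 − c2) + e

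Write q = (c1 − c2)/SD(e), with s = +1 or −1 for order. In units of SD(e), D = τ + s·q + e.

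**Step 2: what cancels.** Take the learning component still present at the four administrations.

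- Level shift between sessions only (1, 1, 0, 0): c1 − c2 = 0 − 0 = 0
- Linear learning (3, 2, 1, 0): c1 − c2 = −1 − (−1) = 0
- Halving at each administration (1, 0.5, 0.25, 0.125): c1 − c2 = −0.5 − (−0.125) = −0.375, so −0.375 for 1PP-first and +0.375 for 3PP-first

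The order term therefore needs a change that differs between sessions. Simple repetition is not enough.

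**Step 3: induced correlation with no true link.** With balanced orders, Cov(Dx, Dy) = qx·qy and Var(D) = 1 + q², so

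r = qx·qy / √[(1 + qx²)(1 + qy²)].

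For equal shifts: 0.0625/1.0625 = 0.06; 0.25/1.25 = 0.20; 0.5625/1.5625 = 0.36; 1/2 = 0.50.

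**Step 4: error rates.** 20,000 simulated trials per row, N = 30, τ = 0, independent residuals:

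| q in both | r (formula) | Pearson, orders pooled | Pearson, order removed | Exact McNemar on signs | Sign agreement |
|---|---|---|---|---|---|
| 0 | 0 | 5.1% | 5.1% | 2.7% | 50% |
| 0.25 | 0.06 | 6.1% | 4.9% | 2.7% | 52% |
| 0.5 | 0.20 | 19.1% | 5.1% | 2.5% | 57% |
| 0.75 | 0.36 | 53.9% | 4.6% | 2.3% | 65% |
| 1.0 | 0.50 | 88.2% | 5.1% | 1.8% | 73% |

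Two further settings:

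- Shift of 0.75 in one measure only: mean r = 0, rejection 4.8%, agreement 50%.
- Shifts of +0.75 and −0.75: mean r = −0.37, rejection 53.8%, agreement 35%.

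**The case against.** **The correlation and the contrast stand in different places.** The correlation is named under Secondary outcomes without its variables; the double difference is defined only under Correlations, where the named test is McNemar. This stands. The Pearson error rates apply only if the correlation is run on those contrasts. They are the only values the article writes out for relating the measures, but the link is an inference.

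**McNemar is not affected.** A reader might infer that the named test will give false positives. It will not: McNemar compares the two marginal proportions, and its rejection rate falls from 2.7% to 1.8% as the common shift grows. What moves is the raw agreement of signs. At q = 0.5 that is about 17 of 30 people instead of 15.

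**Much practice cancels.** This also stands (Step 2). The bias needs a session-dependent change in both measures. Decelerating learning is a natural mechanism for the Stroop task; a parallel change in O2Hb or mood is plausible but not documented.

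**The upper range may be unrealistic for RT.** With 10 trials per type, the RT contrast combines eight 10-trial means, so trial noise alone gives √(8/10) = 0.89 trial SDs. Assuming a trial SD of 150–250 ms, the contrast SD is at least 134–224 ms. Then q = 0.5 needs a session difference of 67–112 ms in the change in interference. Under the halving curve that means 179–298 ms of learnable interference (67/0.375 and 112/0.375). These inputs are assumptions too, but they favour the lower rows of the table for RT.

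**Importance and disclosure.** A reader might take this contrast to be the analysis the article calls crucial. That word opens the preceding paragraph, on the Stroop–fNIRS relation in general, which goes on to an ROI-based repeated-measures ANOVA; the contrast is introduced as an addition. The article also discloses the repetition effect, and a fuller analysis plan may adjust for order. The point therefore concerns only what the article writes out: a formula that pools the orders.

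**Conclusion.** The point holds in a conditional form. As written, the contrast carries session order with opposite sign in the two groups, nothing in the stated analysis removes it, and the planned baseline checks cannot detect it. If both measures change differently in session 1 and session 2, a correlation of these contrasts can be created or masked, and sign agreement can be raised or lowered.

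The size depends on a quantity the documents do not give. The effect is negligible up to about 0.25 SD (6% against a nominal 5%), material at 0.5 SD (19%) and severe only at 0.75 SD or more (54% to 88%).

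The documents do not support the stronger reading that practice in itself produces a false brain–behaviour link whichever association measure is used. Nor does the point touch the mean 1PP-versus-3PP comparison of the primary outcome, which the balanced order protects. It is a worthwhile, low-cost improvement to a secondary analysis.

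A related defect is that the stated contrast is built from incongruent and neutral trials. The TDMS consists of eight mood items and has no such trials, so the contrast cannot be computed for mood as written.

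**What to change.** - **Correlation.** State that the Stroop–fNIRS association is computed on the 1PP-minus-3PP contrasts as a partial correlation given order, or equivalently pooled within order group. With 30 participants the test has 27 degrees of freedom instead of 28.
- **Dichotomised version.** Remove only the order deviation. With order-group means mA (1PP first) and mB (3PP first), set δ = (mA − mB)/2, subtract δ from every 1PP-first value and add δ to every 3PP-first value. Both groups then sit at (mA + mB)/2, so the overall 1PP-minus-3PP mean is kept. Centring each group on its own mean before dichotomising would not do: it removes the condition effect, and the sign would say only whether a person lies above or below the group average.
- **TDMS.** Define the mood contrast as the after-minus-before change in 1PP minus that in 3PP, adjusted for order in the same way.

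Order is fixed by the randomisation and so is already known for everyone. The cost is one degree of freedom and a line or two of analysis code. No new data are needed, and almost nothing is lost if there is no order effect.
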